### Data collection

Feasibility data will be collected during screening, recruitment, eligibility re-assessment and randomisation, during the 12- week intervention period, at 4 months postoperative, at 5- and 7-months postoperative for the THRIVE programme arm, and at 8 months postoperative. Outcome measures will be collected at three timepoints: baseline (preoperative), 4 months postoperative and 8 months postoperative (table 3). Schedule of study procedures. Follow-up questionnaires at 4 and 8 months will be posted to participants who do not attend the in-clinic follow-up research visit. Information from Protocol Deviation forms will be collected ad hoc and patterns and frequencies of deviations will be investigated. Qualitative interviews will be conducted with participants following completion of their intervention. Qualitative interviews with treating clinicians from the THRIVE programme arm will be conducted after they have completed all treatments for all participants.

**Table 3 T3:** Schedule of study procedures

Procedures	Pre-enrolment	Preoperative baseline	Postoperative		4 months follow-up	8 months follow-up	Post-intervention
	Screening	Visit 1	After operation	Intervention period	Visit 2	Visit 3	Qualitative interviews
Potential participant identification and screening	x						
Provision of PIS	x						
Eligibility assessment	x		x				
Informed consent		x					
Outcome questionnaire completion		x			x	x	
Physical assessment by research staff		x			x	x	
Randomisation			x				
Letter sent to GP informing study involvement			x				
Referral to physiotherapy (based on allocated arm)			x				
Trial interventions delivered				x			
Treatment log completed by physiotherapist (THRIVE intervention)				x			
Treatment log completed by physiotherapist (usual care)				x			
Home exercise diary (THRIVE intervention)				x			
Healthcare resource use and family social support diary				x	x	x	
Follow-up phone calls for THRIVE intervention				x			
Adverse events recorded				x	x	x	
Qualitative interviews with selected sample							x

GP, general practitioner; PIS, patient information sheet; THRIVE, tailored physiotherapy rehabilitation.

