### 3fRandomisation and allocation concealment

After the participants have undergone rTHA, the research clinician will re-assess their eligibility to participate. Participants may become ineligible if they require a further revision surgery or if their status and/or discharge destination has changed and impacts participation in outpatient physiotherapy. Eligible patients will be randomised by an unblinded research team member in a 1:1 ratio between the intervention and usual care groups using a web-based centralised randomisation database (SealedEnvelope), which will be managed by the trial manager. Stratified permuted block randomisation will be used, with stratification by sex and site. Blocks will be of random sizes. The statistician will oversee the allocation sequence produced by SealedEnvelope; no other members of the team will have access to it. By the nature of the intervention, patients and clinicians cannot be blinded to treatment once allocation has occurred. The research clinician collecting data from follow-up research visits will be blinded to treatment allocation. Additionally, data analysis will be conducted in a blinded fashion. Participants from both arms will complete the standard postoperative care pathway before being allocated to the treatment arm they were randomised to and scheduled for an outpatient physiotherapy appointment approximately 2–4 weeks post-operatively.

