### Study arms

#### Comparator arm/usual care

Participants will receive a standardised usual care programme. Having completed consultations with stakeholders within centres that perform revision operations, usual care has been standardised to comprise an initial evaluation by a physiotherapist with a home exercise programme (approximately 60 min) and up to two follow-up sessions (30 min each) within 12 weeks, delivered in-person or remotely (depending on participant preference). This falls within the recommendation of the NICE guidelines for THA rehabilitation.

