#### Intervention arm/tailored physiotherapy rehabilitation programme

Our tailored physiotherapy rehabilitation (THRIVE) programme will involve targeted progressive strengthening, gait re-training and education. The delivery of the physiotherapy elements will be underpinned by the Capability, Opportunity, Motivation-Behaviour (COM-B) model and include evidence-based behaviour change techniques to encourage adherence.^21^ Owing to the complexity of the patient group, who will present with multiple co-morbidities and environmental factors to account for, the intervention will be delivered flexibly while maintaining the primary tenets of the intervention.^22^ In our theory of change model, we outline the interactions between problems in this patient group, our tailored physiotherapy intervention, the mechanism of change and the intended participant outcomes (figure 2). The THRIVE programme will comprise an in-person physiotherapy evaluation (approximately 60 min) and 5–8 follow-up sessions (30 min each) delivered in-person or remotely over a 12-week period. Additionally, there will be two follow-up phone calls (15 min each) 5 and 7 months postoperatively.

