### Ethics and dissemination

A UK Research Ethics Committee has approved this study (West of Scotland REC 25/WS/0080). All participants will provide their informed consent to participate in the study. The study will investigate the feasibility of conducting this trial and will also examine closely the practical, operational and safety barriers that arise. This is a diverse clinical population, with high healthcare utilisation, and many revision operations are performed at regional hubs. Specialist referral pathways might be barriers for recruitment since outpatient physiotherapy is delivered at the surgical centre where we can ensure expertise and adequately experienced musculoskeletal physiotherapists. At one study site, we are trialling the hub-and-spoke model. Participants who live ‘out-of-area’ can receive their standardised usual care from their local community provider. This will allow us to understand if the model has the potential to increase recruitment, decrease clinical load on the secondary care centre, and if participants value receiving physiotherapy more locally. As we analyse our primary outcomes, which are recruitment and retention rates, we will focus on these potential issues and probe them in the qualitative interview study.

Trial results will be reported in the trial registry, published in an open-access academic journal, presented at relevant physiotherapy and orthopaedic conferences and shared in an accessible summary with the trial participants. The final report will detail amendments to the study protocol. The final manuscript will be reported according to the^47^ statement extension to randomised pilot and feasibility trials.^47^

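### Table 3 starts adverse event recording after randomisation, and the two arms have very unequal treatment contacts at which events could be noted

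*Protocol article*

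**What the plan says.** The schedule in the Data collection section (Table 3) has one row for safety, "Adverse events recorded", shared by both arms. It is marked under the intervention period, Visit 2 (4 months) and Visit 3 (8 months). It is blank under After operation, the column that carries the second eligibility check, randomisation and the physiotherapy referral.

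The section on randomisation and allocation concealment gives the order of events. "After the participants have undergone rTHA, the research clinician will re-assess their eligibility to participate", and those still eligible are then randomised. "Participants from both arms will complete the standard postoperative care pathway before being allocated to the treatment arm they were randomised to", and they are then "scheduled for an outpatient physiotherapy appointment approximately 2–4 weeks post-operatively". The same section says that patients and treating clinicians cannot be blinded, whereas the research clinician who collects follow-up data is blinded.

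The contact schedules differ by arm. THRIVE has an evaluation, then "5–8 follow-up sessions (30 min each) delivered in-person or remotely over a 12-week period", then "two follow-up phone calls (15 min each) 5 and 7 months postoperatively". Usual care has an evaluation and "up to two follow-up sessions (30 min each) within 12 weeks".

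The Safety reporting section makes the principal investigators responsible for assessing events and refers to Good Clinical Practice for definition and reporting. It does not say who asks about events or at which contacts. The Ethics and dissemination section says that the study will "examine closely the practical, operational and safety barriers that arise".

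**The concern.** Two separate issues arise from the same table row.

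The first is the start of recording. A randomised participant belongs to the trial population from randomisation, and the article says that analyses follow intention-to-treat principles. On the printed schedule, an event after randomisation but before the first appointment has no recording point. Such an event may be the reason a participant never starts treatment, which makes it relevant to a study that wants to know about safety barriers.

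The second is unequal opportunity to record. In the intervention period column, the only staff contacts marked are treatment delivery, with the physiotherapists' logs, and the THRIVE phone calls. No research assessment is marked there. If events are captured in that column through the treating physiotherapists, THRIVE participants have several times as many occasions to mention one. The two calls also reach THRIVE participants at 5 and 7 months, when usual care has no scheduled contact. A higher THRIVE count could then arise with no true difference, and it could colour the view of safety taken into a definitive trial.

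**Working it through.** The plan gives no figure for adverse events, so there is none to reproduce. The check reads the schedule against the text and counts contacts.

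**1. The unrecorded window.** It runs from randomisation to the first outpatient appointment. The appointment is at about 2 to 4 weeks after surgery. Randomisation is also after surgery, on a day not stated, so the window is at most about 2 to 4 weeks. As a share of the 8 postoperative months (8 × 52.18 / 12 = 34.8 weeks), the upper limit is 2 / 34.8 = 6% to 4 / 34.8 = 11%. Both arms follow the same care pathway and the same blank cell in this window, so the omission is symmetrical.

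**2. Contacts per participant,** from the two study-arm sections and Table 3:

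| | THRIVE | Usual care |
|---|---|---|
| Evaluation | 1 | 1 |
| Follow-up sessions | 5 to 8 | 0 to 2 |
| Phone calls | 2 | 0 |
| Treatment contacts | 8 to 11 | 1 to 3 |
| Research visits (4 and 8 months) | 2 | 2 |
| All contacts | 10 to 13 | 3 to 5 |

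With usual care at its maximum, the ratio of treatment contacts is 8/3 = 2.7 to 11/3 = 3.7. With the research visits included, it is 10/5 = 2.0 to 13/5 = 2.6.

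**3. What this could do to counts.** Assume that an event has probability q of being captured at each contact, independently, with the same true event rate in both arms. The documents do not give q. The probability of capture over k contacts is 1 − (1 − q)^k. The table takes usual care at its maximum of 5 contacts, which is the comparison most favourable to the plan.

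| q | Usual care, k = 5 | THRIVE, k = 10 | THRIVE, k = 13 | Apparent ratio |
|---|---|---|---|---|
| 0.1 | 0.410 | 0.651 | 0.746 | 1.59 to 1.82 |
| 0.2 | 0.672 | 0.893 | 0.945 | 1.33 to 1.41 |
| 0.3 | 0.832 | 0.972 | 0.990 | 1.17 to 1.19 |
| 0.5 | 0.969 | 0.999 | 1.000 | 1.03 |

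A usual-care participant who has only the evaluation and the two research visits (k = 3) would have capture 1 − 0.8³ = 0.49 at q = 0.2, so the ratios would be larger there.

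The model is crude. It treats every contact as able to detect every event, including contacts before the event happened, and gives a routine session the same chance as a visit scheduled to record events. It shows the direction and the possible range only.

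**4. After the fix.** If the by-arm summary rests only on the contacts common to both arms, the count is 2 versus 2, and the difference in opportunity disappears for participants who attend or return the questionnaire.

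**The case against.** The strongest reply is that the ascertainment route is inferred. The article nowhere says that events are elicited at sessions or calls. It is a condensed account, and version 4.0 of the full protocol, which is not shown here, may settle the matter. This stands, and it is why the second issue is conditional. The blank cell under After operation is different: the article prints a schedule, and that schedule fixes a start after randomisation. One could read the intervention period column as opening at randomisation, but the Data collection text lists randomisation and the 12-week intervention period as separate steps.

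A reader might infer that events explaining non-attendance are lost. The documents do not support that. The Feasibility outcomes section has reasons for decline or loss to follow-up logged at each stage from screening onward, so a reason should exist for a participant who never starts. What may be missing is its entry as an adverse event assessed for seriousness and relatedness.

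A reader might also infer that the arms are not comparable on safety. That does not follow either. The early gap is the same in both arms and precedes either programme. Recording at 4 and 8 months is scheduled in both arms, at visits where a blinded clinician collects the data, and can pick up earlier events. These visits are not a complete safeguard: non-attenders are sent questionnaires, and the article does not say whether these ask about adverse events.

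Finally, no by-arm comparison of adverse events is specified, no formal assessment of treatment effect is planned, and Table 4 has no safety criterion. This limits the consequence to descriptive counts.

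**Conclusion.** The point holds in a limited form and is minor. On the printed schedule, events between randomisation and first physiotherapy are not scheduled for recording in either arm. This is a completeness gap of at most about 2 to 4 weeks, and it gives no reason to doubt comparability.

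Unequal ascertainment is a risk and not an established fault. It rests on two assumptions: that events are picked up at treatment contacts, and that the chance of capture per contact is low. Comparing 10 to 13 THRIVE contacts with 5 in usual care, the apparent ratio with no true difference is about 1.8 at the top (assumed capture 10%) and 1.03 at the bottom (assumed capture 50%), so it could be material or negligible. No planned test or progression rule depends on it. What could be affected is the descriptive picture of safety that informs a definitive trial.

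**What to change.** - In Table 3, mark adverse events from randomisation in both arms.
- At the existing 4- and 8-month visits, ask both arms the same structured question about events since the last research visit. At 4 months, word it as since randomisation, because the previous research visit is the preoperative baseline.
- Put the same question in the questionnaire posted to participants who do not attend.
- Use those answers for any safety summary by arm, and list events noted at treatment contacts separately.

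The cost is one extra mark in the schedule, one standard question at two existing visits and in the postal form, and a second listing in the report. Slightly more events will be recorded, including ordinary postoperative ones.

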### Data management

Data will be collected using a mix of electronic and paper forms. Data will be pseudonymised using patient identification and stored on NHS servers in encrypted files. Data will be entered centrally into a REDCap database where data provenance will be documented. Qualitative interviews will be transcribed, de-identified and pseudonymised. Participant contact details will be deleted when no longer required as part of the study (following posting of the summary of study results). This will be within 12 months of the end of the study. Additional information regarding data management can be found within the Data Management and Access Plan.

### Statistics and data analysis

#### Sample size calculation

As this is a feasibility study that does not aim to assess treatment effects, we have not undertaken a formal power sample size calculation. A minimum of 60 participants (≥30 in each arm) will be recruited, as recommended to estimate key design parameters in a feasibility RCT and establish the study sample size for a definitive trial.^44^ The qualitative sub-study will include up to 24 participants from the main trial (up to 16 from the THRIVE intervention group and up to eight from the usual care group). Additionally, we will interview up to eight clinicians who delivered the THRIVE intervention. These qualitative samples are aligned with interpretive qualitative research methods that do not rely on statistical representation. Our sampling strategy will be influenced by the principles of Information Power.^45^

#### Statistical analysis plan

Primary analysis will evaluate the feasibility of conducting the study. The feasibility outcomes (eg, recruitment rate, consent proportion, physiotherapy session attendance and retention rate) will be described by randomisation group using frequency, proportions and figures, where appropriate.

We will use progression criteria to assess the feasibility of a future definitive trial using a ‘traffic light’ system (table 4. Trial progression criteria). These quantitative progression criteria will be considered in combination with qualitative findings to guide decision making and trial design. Green (go) indicates feasible with the current procedures, amber (amend) indicates feasible if there is modification to one or more components of the protocol and red (stop) indicates a definitive trial would not be feasible without significant changes to protocol.

**Table 4 T4:** Trial progression criteria

Criteria	Green/go	Amber/amend	Red/stop
Recruitment	**≥60** eligible participants recruited within 10 months	**45-59**	**<45**
Intervention fidelity	**≥75%** of participants receive the allocated intervention per protocol	**50%–74%**	**<50%**
Adherence	**≥75%** of THRIVE intervention participants have at least five follow-up sessions delivered	**50%–74%**	**<50%**
Outcome data completion rate	**≥80%** of participants have 8-month outcome data	**≥60%–79%**	**<60%**
Outcome measure use in full trial	**Two or more** outcomes suitable for full trial	**One outcome** suitable for full trial	**No outcomes** suitable for full trial
Intervention implementation	Delivery of intervention judged **strongly feasible** by qualitative data	**Feasible**	**Possibly feasible**

THRIVE, tailored physiotherapy rehabilitation.

The characteristics of the randomised groups will be described using mean and SD, or frequency and proportions, as appropriate.

The outcome assessments, including patient-reported outcome measures and performance-based measures, will be reported in a descriptive fashion, with no formal assessment of treatment effect between groups since this is a feasibility study. We will summarise outcomes overall and in each group. Completeness and variability of the outcome measures will be used together as a guide to help determine the best outcome for a future main study. We will visualise the change in outcomes over time within groups using plots. All analyses will follow intention-to-treat principles. We will report the amount of missing data for each outcome and summarise patterns of missingness.

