### Objectives

The primary objective of this feasibility study is to estimate recruitment and retention within the study. The secondary objectives are to (1) appraise adherence to the intervention, (2) evaluate intervention fidelity, (3) evaluate outcome measures for a full trial, (4) confirm a definitive primary outcome for a full trial and (5) explore the experience of participants in the trial and clinicians delivering the intervention (table 1).

**Table 1 T1:** Study objectives and outcome measures

	Objectives	Outcome measures
Primary	To analyse (a) recruitment to the study and (b) retention in the study.	Screening logs, eligible patients consented (%) and randomised (%). Logs of data collection (retention rate)
Secondary	To appraise adherence to the intervention.	Physiotherapy session attendance, retention rate and qualitative interviews.
	To evaluate intervention fidelity.	Delivery of all three main components of the intervention (exercise progression, gait re-training and education) as monitored on treatment logs and qualitative interviews.
	To evaluate outcome measures for a full trial.	Assessment of the completion rate of the patient-reported outcome measures and performance-based outcome measures and qualitative interviews with patients and physiotherapists.
	To confirm a definitive primary outcome for a full trial.	Completion rate of expected primary outcome for future full trial: Oxford hip score
	To explore the experience of participants in the trial and physiotherapists delivering the intervention.	Qualitative interviews

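### As plainly read, the Table 4 fidelity criterion covers both arms, conflicts with Table 1, and can turn green with THRIVE delivery below its own 75% cut-off

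*Protocol article*

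**What the plan says.** Table 4 (Statistical analysis plan) grades fidelity by the percentage "of participants receive the allocated intervention per protocol": green at 75% or more, amber at 50% to 74%, red below 50%. The next row, adherence, uses the same cut-offs but names its denominator: the percentage "of THRIVE intervention participants have at least five follow-up sessions delivered".

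Table 1 (Objectives) gives the measure for the fidelity objective as "Delivery of all three main components of the intervention (exercise progression, gait re-training and education) as monitored on treatment logs", together with qualitative interviews. The section on the intervention arm shows whose components these are: the THRIVE programme "will involve targeted progressive strengthening, gait re-training and education".

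The section on the comparator arm describes usual care as an initial physiotherapist evaluation with a home exercise programme and "up to two follow-up sessions (30 min each) within 12 weeks". No minimum number of follow-up sessions is set.

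The Statistical analysis plan section also says that feasibility outcomes will be described by randomised group and that the traffic lights will be weighed together with the qualitative findings. It states no separate fidelity cut-off for either arm.

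**The concern.** The fidelity row differs from the fidelity objective in two ways. Its denominator is all participants, where Table 1's definition fits only those allocated to THRIVE. Its numerator is receipt of whichever intervention was allocated, where Table 1 asks for three named THRIVE components.

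The two arms are not equally hard to deliver. THRIVE is an in-person evaluation, five to eight follow-up sessions, three content components and two later phone calls. Usual care is one evaluation with a home programme and at most two follow-ups. If both count equally, the less demanding arm supplies half the denominator and can lift the combined percentage over the cut-off.

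A feasibility trial needs to learn whether the new programme can be delivered as designed. A green light on fidelity could be shown when THRIVE delivery, taken alone, lies in the amber band. If the row can be read either way, the same data can also be green or amber depending on a choice made after they are seen.

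**Working it through.** **Inputs.** Sample size: "A minimum of 60 participants (≥30 in each arm) will be recruited" (Sample size calculation). Allocation: 1:1 (Randomisation and allocation concealment). Cut-offs: 75% and 50% (Table 4). Usual-care fidelity is not given in the article, so it is assumed and varied from 80% to 100%. The cut-offs were chosen rather than derived, so there is no figure of the plan's own to reproduce.

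**Counts needed for green.** Both arms combined: 0.75 × 60 = 45 of 60. THRIVE only: 0.75 × 30 = 22.5, so 23 of 30 (76.7%).

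**Smallest THRIVE count that gives a combined green** = 45 − usual-care count:

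| Usual care per protocol | THRIVE needed | THRIVE fidelity |
|---|---|---|
| 30/30 (100%) | 45 − 30 = 15 | 50% |
| 27/30 (90%) | 45 − 27 = 18 | 60% |
| 24/30 (80%) | 45 − 24 = 21 | 70% |

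Each of these THRIVE results would be amber if the cut-offs were applied to THRIVE alone.

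**The red boundary.** Combined red needs fewer than 0.50 × 60 = 30. With usual care at 30/30, even 0/30 in THRIVE gives 30/60 = 50%, which is amber. With usual care at 27/30, 3/30 in THRIVE (10%) is enough to avoid red.

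**Chance of green.** Let A ~ Bin(30, p_T) be the THRIVE count and U ~ Bin(30, p_U) the usual-care count, independent. The combined rule is P(A + U ≥ 45), summed exactly over A. The THRIVE-only rule is P(A ≥ 23).

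| True THRIVE fidelity | p_U = 100% | 95% | 90% | 80% | THRIVE-only rule |
|---|---|---|---|---|---|
| 60% | 90% | 76% | 57% | 24% | 4% |
| 50% | 57% | 37% | 22% | 6% | 0.3% |

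**Direction.** The combined rule asks less of THRIVE than 75% whenever usual-care fidelity is above 75%. It can also err the other way: usual care at 18/30 with THRIVE at 26/30 (87%) gives 44/60 = 73%, so a well-delivered THRIVE would show amber.

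**The case against.** The strongest reply is that combining the arms is inferred. Nowhere does the article say that they go into one percentage, and Table 1's definition can be applied only to THRIVE, so the two tables read together could support a THRIVE-only denominator. This stands as a limit on how firmly the point can be put. It does not remove the point: the row speaks of the allocated intervention and names no arm, while the next row does name one. If THRIVE alone was meant, the row needs the same edit.

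A reader might go further and infer that the plan will pass THRIVE when only half its participants received it. The article does not support that as a general statement. The 50% figure needs perfect usual-care fidelity, and the article neither gives a rate nor defines per-protocol receipt for usual care. That a single attended evaluation would count is an inference from the absence of a minimum. Usual-care delivery could fall short, for instance through contamination or out-of-area delivery by community providers. At 80%, THRIVE must reach 70%, close to the stated cut-off.

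Three safeguards deserve weight. Description by arm would make a THRIVE shortfall visible. The lights are weighed with qualitative findings, and a separate row judges implementation from them. The adherence row is restricted to THRIVE and would catch a shortfall caused by missed sessions. None of these changes the fidelity light, and the adherence row counts sessions, not content: five sessions without gait re-training satisfy it and fail Table 1's definition.

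Fidelity of the comparator is also a fair feasibility question, since usual care was standardised for this trial. That argues for measuring it separately. Finally, the full protocol is cited but not shown and may define per-protocol receipt. That would settle the numerator, but the mismatch between Tables 1 and 4 stands in the published text.

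**Conclusion.** The point holds in this form: the fidelity criterion, as plainly read, covers both arms and conflicts with the definition of fidelity in Table 1. On that reading, with 30 per arm, green is compatible with THRIVE fidelity of 50% to 70% across assumed usual-care fidelity of 100% down to 80%. If true THRIVE fidelity is 60%, the chance of green across that range is 90% down to 24%, against 4% under a THRIVE-only rule.

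These sizes rest on the combined reading, on exactly 30 per arm, on independent binomial counts and on the assumed usual-care rates. The conflict between the tables rests on none of them. The article does not support saying that combination is an explicit rule, or that half delivery in THRIVE will generally pass. The other safeguards lessen the practical harm but leave this criterion unable to answer its own question reliably.

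**What to change.** Reword the fidelity row so that the existing cut-offs apply to participants randomised to THRIVE, for example: green if at least 75% of participants randomised to THRIVE had all three components (exercise progression, gait re-training and education) delivered per protocol, as recorded on the treatment log; amber from 50% to below 75%; red below 50%. Keep the per-protocol requirement, so that a single logged entry for each component does not pass by default.

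Report usual-care fidelity separately from its own treatment logs, together with any THRIVE component recorded there as contamination. If usual-care delivery is also meant to be a progression criterion, give it its own row and do not combine it with THRIVE.

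The cost is one table row, or two if usual care gets its own. Table 3 already schedules treatment logs in both arms, so no new data are needed. Recruitment began in September 2025, so the change should be made and dated before fidelity data are reviewed. The downside is that green on fidelity becomes harder to reach whenever usual-care fidelity exceeds THRIVE fidelity.
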